The following variables will be tested as potential predictors or moderators of intervention response: demographic variables (age, gender, educational level), motivation to change (importance, ability and readiness to change), severity of ED symptoms (SEED, EDE-Q) [23,37], severity of symptoms of depression and anxiety (PHQ-4) [31], early working alliance (SRS) [38], and compliance.

Mediator variables and their corresponding dependent variable will be measured frequently throughout this study, at T0 and T1, as well as once every two weeks in between T0 and T1. The variables repetitive negative thinking (PTQ) [32] and symptoms of depression and anxiety (PHQ-4) [31] will be tested as mediators of intervention outcome, being symptoms of ED as measured by the SEED [23].

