### Sample size

The sample size calculation is based on an expected small between-group effect size (Cohen’s *d* = 0.32) [45]. The calculation is conducted by the software program Power Analysis and Sample Size (PASS, 2008). The primary analysis will concern the hypothesis that the average post-intervention level of eating pathology in the waiting list control condition is higher than the average level of eating pathology in the three active intervention conditions. Assuming an alpha of 0.05 and a power of 0.80 (β-1) in a one-way ANOVA study, we need sample sizes of 79 participants in each of the four groups whose means are to be compared using a planned comparison. Taking into account a baseline variable (e.g., T0 assessment) for which we assume a Pearson correlation of 0.5 with the outcome variable, and thus explaining 25% of the variance of the outcome variable, the sample size per group can be reduced by 25% and is thus calculated as 0.75 × 79 = 60 per group. In order to account for dropout, recently reviewed to be approximately 30% for Internet-based interventions [46], the definitive number of participants we will need to recruit is 10/7 × 60 = 86 participants per group, resulting in 344 in total.

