### Statistical analyses

All statistical analyses will be performed in SPSS version 19. A two-tailed significance level of *α* = 0.05 will be used throughout the analyses. Both intent-to-treat and completers analyses will be conducted. Intent-to-treat analyses will include every participant who is randomly allocated to the intervention, regardless of withdrawal or deviation from the protocol [47]. Someone will be considered a completer in case he/she has completed both T0 and T1 assessments, and at least five monitoring assessments.

Pre-treatment differences between the conditions will be investigated using *χ*^*2*^ tests for categorical variables and ANOVAs for continuous variables. Linear mixed model analyses will be used to investigate the effectiveness and maintenance effects of Featback. Time contrasts will be created by means of dummy-coding. Within- and between-group effect sizes (Cohen’s *d*) [48] will be calculated based on the pooled standard deviation. As recommended by Frazier, Tix and Barron [49], potential categorical predictor or moderator variables will be dummy coded, and potential continuous predictor or moderator variables will be standardized. A significant two-way interaction between predictor and time indicates a predictor effect. A significant three-way interaction between time, condition and moderator, indicates a moderator effect. Significant moderator effects of continuous variables will be interpreted by dichotomizing the moderator variable into subgroups of participants who score either low or high (e.g., below or above the sample mean) on the moderator variable. Separate mixed model analyses will then be repeated to examine interactions between condition and time within the low and high subgroups.

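### Significant continuous moderators are interpreted by a low/high split with separate models, when the interaction model already fitted gives the conditional effects directly and consistently

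*Protocol article*

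**What the plan says.** The Background section makes predictors, moderators and mediators the second aim. The Assessments section introduces the candidates with "The following variables will be tested as potential predictors or moderators of intervention response" and lists several that are continuous or nearly so: age, motivation to change, SEED, EDE-Q, PHQ-4, SRS and compliance.

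The Statistical analyses section sets out three steps.

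1. Scale: "potential continuous predictor or moderator variables will be standardized".
2. Test: "A significant three-way interaction between time, condition and moderator, indicates a moderator effect", at the general two-sided 0.05 level.
3. Interpretation: significant continuous moderators are to be interpreted by "dichotomizing the moderator variable into subgroups of participants who score either low or high", with the sample mean given as an example of the cut, after which "Separate mixed model analyses will then be repeated to examine interactions between condition and time within the low and high subgroups".

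No step is described in which conditional effects are estimated from the fitted interaction model.

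**The concern.** The test and its interpretation use two different models. The test uses the whole sample and the full scale of the moderator. The interpretation uses a two-level version of the moderator and fits each level separately.

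This has three consequences for the second aim.

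- **Within-half variation is ignored.** A participant just above the cut is treated like one at the extreme, and the moderator trend within each half becomes residual noise.
- **The cut depends on the sample and is not fully fixed.** The sample mean appears only as an example. It divides a symmetric moderator about evenly, but with a skewed one (exponential, for illustration) only about 37% fall in the high group. Low and high would then mean something different in another sample.
- **The two sets of results can conflict.** Testing condition by time inside each half invites the reading that the intervention works in one half and not in the other. A significant result in one half and a non-significant result in the other does not test the difference between them.

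**Working it through.** **Figures in the plan.** The article gives no number for the moderator analysis, so there is none to reproduce. From the Sample size section I take the evaluable number, the baseline correlation and the effect size. The article's arithmetic from its starting value of 79 follows: 0.75 × 79 = 59.25, taken as 60 per group; 60 × 10/7 = 85.7, taken as 86 per group; 4 × 86 = 344. The 79 itself is not at issue here.

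**Inputs**
- 60 evaluable per group, waiting list against three active arms: 60 against 180.
- Baseline correlation 0.5, so the residual variance is 1 − 0.25 = 0.75 (outcome SD 1).
- Effect 0.32 at the mean of the moderator.
- Assumed, because the article gives none: a normal moderator unrelated to outcome in the waiting list arm, and a linear interaction *b* of 0.2, 0.3 or 0.4 outcome SD per moderator SD.

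**Full model.** At a moderator value of *a* SDs, the variance of the condition effect is about 0.75 × (1/60 + 1/180) × (1 + *a*²) = 0.01667 × (1 + *a*²).
- *a* = 0: SE = √0.01667 = 0.129.
- *a* = √(2/π) = 0.798, the mean of each half: SE = 0.129 × √1.637 = 0.165.
- *a* = 1: SE = 0.129 × √2 = 0.183.

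**Half-sample model.** This has 30 against 90. The trend left inside each half of the active arms adds to the residual variance. Within-half moderator variance is 1 − 2/π = 0.363 and active participants are 3/4 of the sample, so the residual variance is about 0.75 + 0.75 × 0.363 × *b*², and SE = √[residual variance × (1/30 + 1/90)].
- *b* = 0.2: √(0.761 × 0.0444) = 0.184.
- *b* = 0.3: √(0.775 × 0.0444) = 0.186.
- *b* = 0.4: √(0.794 × 0.0444) = 0.188.

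**Simulation**, restricted to runs with a significant interaction, because only those trigger the follow-up:

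| *b* | Full model, half mean (±0.8 SD) | Full model, ±1 SD | Half-sample model |
|---|---|---|---|
| 0.2 | 0.166 | 0.183 | 0.184 |
| 0.3 | 0.166 | 0.183 | 0.186 |
| 0.4 | 0.166 | 0.184 | 0.188 |

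At the same moderator value, interval widths compare as 0.184/0.166 = 1.11 to 0.188/0.166 = 1.13. Against ±1 SD the ratios are 0.184/0.183 = 1.01 to 0.188/0.184 = 1.02.

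**Consistency with the test.** Among runs with a significant continuous interaction, the difference between the two half-sample effects was itself non-significant in about 46%, 35% and 22% to 25% of runs for *b* = 0.2, 0.3 and 0.4 at 60 per group. At 86 per group the figures were about 38% to 41%, 28% and 14% to 15%. The ranges are across repeat runs.

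**The case against.** The other side has several good points.

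- **The test is sound.** A reader might apply the known result that a mean split of a normal moderator keeps 2/π, or 64%, of the information on a linear interaction, and infer a loss of power to detect moderation. The article does not support that: the interaction is tested on the continuous scale, and its error rate and power are untouched. The 64% describes a test that the plan does not run.
- **No one is excluded.** A reader might infer that data are thrown away. Both halves are analysed, and nothing says that the continuous interaction estimate will go unreported. What is lost is information within each half, in a follow-up step.
- **The precision gain is local.** A reader might expect narrower intervals wherever the full model is used. At ±1 SD there is almost no difference. For the same reason, it does not follow that a half would be called non-responding merely because it is small: an effect at ±1 SD from the full model is about as imprecise.
- **The comparison of significant with non-significant is not a stated rule.** The difference has already been tested before the split is made. The wording invites the misreading but does not prescribe it.
- **The simulation favours the linear model and simplifies the repeated-measures analysis.** The simplification is real. The linearity point carries little weight, because the planned interaction test already assumes a linear trend.

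It can also be said that a condensed article may leave such probing to a fuller plan. That would answer a silence. Here the split and the separate models are stated outright.

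**Conclusion.** The point stands as a modest improvement to the follow-up of a secondary aim. It does not touch the primary comparison, the sample size or the validity of the moderation test.

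The stated follow-up is inferior to what the fitted model already provides. For effects at the half means its intervals are 11% to 13% wider. At ±1 SD the advantage of the full model is an estimate at a defined moderator value that cannot contradict the interaction test, not a narrower interval. The split also rests on a cut that varies with the sample and is not fully fixed.

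The figures assume 60 evaluable per group, a residual variance of 0.75, a normal moderator with no relation to outcome in the waiting list arm, a linear interaction of 0.2 to 0.4 per SD, and a single between-group contrast in place of the full mixed model over time. A moderator that also predicts outcome in the waiting list arm in the same direction would raise the half-sample standard errors somewhat further, unless it is adjusted for within each half.

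**What to change.** In the Statistical analyses section, replace the low/high split and the separate subgroup models with this rule: for each significant continuous moderator, report the condition-by-time effects with 95% confidence intervals from the full-sample model with the continuous moderator, at moderator values stated in advance, for example the mean and ±0.8 SD or ±1 SD. A low/high plot may stay, labelled as illustration only.

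The estimates are linear combinations of coefficients from a model that will be fitted anyway, so no data, sample size or primary analysis changes. The small cost is continued reliance on linearity, which the planned interaction test already requires.

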The primary aim of the current study will be to investigate the effectiveness of (the different components of) Featback. The second aim is to investigate potential predicting, moderating, and mediating variables in order to gain insight into when or for whom this intervention works, as well as how it works. The third aim of this study is to report on the practical experiences of Featback, such as the user satisfaction and the (intensity of) use of the different components. Finally, the fourth aim of this study is to examine the cost-effectiveness of Featback.

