### Ethical precautions and crisis management

Coaches are instructed to refer participants who report suicidal ideation to the website 113Online (http://www.113online.nl); this organization aims to prevent suicide. It employs psychologists, psychiatrists, and a large group of fully trained volunteers, who are accessible via telephone and chat day and night. Furthermore, action is taken when screening or monitoring data show that a participant’s BMI is equal or lower than 15 or when a participant reports being engaged in self-induced vomiting, binge eating or use of laxatives at least once a day over the past four weeks. Subsequently, in case a participant is in condition one (basic Featback) or four (WLC, only screening data), the Featback team will send an e-mail with the message that his/her test scores indicate severe ED symptoms and that if he/she is not yet in treatment, we strongly recommend seeking professional help. In case a participant is in condition two or three, the Featback team will check whether one or more support sessions are planned for the week, and if not, will contact the participant with the message that we believe that his/her test scores indicate severe ED symptoms and that we strongly recommend to make use of one or more support sessions. In these support sessions, the alarm signals will function as a starting point for the conversation and participants will be stimulated to seek professional help. In case participants do not sign in for any support session during the week, the Featback team will send an e-mail as described for participants in condition one.

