A cross-lagged panel design will be used to determine whether changes in mediator variables predict changes in ED symptoms, and not vice versa, as described by Burns et al. [50]. For all outcome and mediator variables, residualized change scores will be calculated for baseline (T0) to mid-intervention (week 4), as well as for mid- (week 4) to post-intervention (T1: week 8). Hereafter, hierarchical regressions will be performed, with mid- to post-intervention standardized change of the primary outcome measure as dependent variable, pre- to mid-intervention standardized change of the primary outcome measure, and mid- to post-intervention standardized change of the mediator variable as independent variables in the first step. In the second step, pre- to mid-intervention standardized change of the mediator variable will be entered into the regression equation. In addition, the inverse association (whether changes in the primary outcome variable predict changes in the mediator variable) will be tested and should not be significant.

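### The cross-lagged regressions show which change comes first among Featback users; alone they cannot show that PTQ or PHQ-4 mediates the effect of Featback

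*Protocol article*

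**What the plan says.** The Background gives the second aim as gaining "insight into when or for whom this intervention works, as well as how it works". Under Assessments, PTQ and PHQ-4 "will be tested as mediators of intervention outcome, being symptoms of ED as measured by the SEED". They are measured at T0 and T1, "as well as once every two weeks in between T0 and T1".

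Under Statistical analyses, a cross-lagged panel design is to be used "to determine whether changes in mediator variables predict changes in ED symptoms, and not vice versa". Change is split at the middle of the intervention: "residualized change scores will be calculated for baseline (T0) to mid-intervention (week 4"), and again from week 4 to T1. The dependent variable is late change in the outcome. Step one enters early outcome change and late mediator change. Then: "In the second step, pre- to mid-intervention standardized change of the mediator variable will be entered into the regression equation". The only further requirement is that the reverse regression, from outcome change to mediator change, is not significant.

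Condition appears in the moderator model of the same section, as a three-way interaction with time and moderator. It does not appear in the mediation paragraph.

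**The concern.** Mediation of an intervention needs two links: the intervention changes the mediator, and the mediator then changes the outcome. The mediation paragraph addresses only the second, in observational form. People who receive no Featback may also find that rumination or low mood eases before eating symptoms do. Such a natural course satisfies the planned criterion as well as a true mechanism would.

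The waiting list (WLC) cannot serve as a check inside this analysis if it has no week-4 values, and it appears to have none. Weekly monitoring is described as a component of basic Featback. The section on ethical precautions separates the data sources when it says "in case a participant is in condition one (basic Featback) or four (WLC, only screening data").

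At stake is the conclusion on a stated secondary aim: PTQ or PHQ-4 could be reported as how Featback works when Featback does not move either. The primary effectiveness comparison is not affected.

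**Working it through.** **Figures in the plan.** The article gives no figure for the mediation analysis. Its sample size section supplies the number of participants: 0.75 × 79 = 59.25, taken as 60 per group; 10/7 × 60 = 85.7, taken as 86; 4 × 86 = 344. The three active arms therefore hold 3 × 86 = 258 recruited and 3 × 60 = 180 after the 30% dropout allowance. Alpha is 0.05, two-tailed.

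**Simulating the full criterion.** The planned regressions were run on simulated data in which allocation affects nothing (2,000 trials per setting). Each four-week step was:

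- mediator(next) = 0.6 × mediator + error
- symptoms(next) = 0.6 × symptoms + b × mediator + error

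The stability of 0.6, a baseline correlation of 0.5 and an error correlation of 0.2/0.6 = 0.33 are assumptions; the documents give none of them. Here b is the natural cross-lag from mood to later symptoms. Residualised, standardised changes were formed for T0 to week 4 and week 4 to T1. The criterion was met if the step-two coefficient had p < 0.05 and the reverse test had p ≥ 0.05.

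| b | n = 180 | n = 258 |
|---|---|---|
| 0 | 5% | 6% |
| 0.1 | 24% | 31% |
| 0.2 | 64% | 80% |
| 0.3 | 88% | 92% |
| 0.4 | 93% | 93% |

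The reverse test removes little: at n = 180 and b = 0.2, step two alone is significant in 69% and the full criterion is met in 64%. A one-directional natural sequence is exactly what that test lets through.

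**Would a condition term help?** At n = 180 and b = 0.2, step two is significant in 69% of trials both without and with condition dummies. As a covariate, condition leaves the coefficient for mediator change where it was.

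**Would a condition effect on the mediator help?** The run also required a significant difference between arms in early mediator change, together with a significant step two (condition dummies included, reverse test not applied). False claims then fell as follows, over b = 0 to 0.4:

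- three active arms, n = 180: 0.4% to 4.6%
- three active arms, n = 258: 0.3% to 5.5%
- four arms, n = 240, supposing the WLC were measured at week 4: 0.2% to 5.3%

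The reason is general. When allocation affects nothing, a 5% test of condition on the mediator succeeds about 5% of the time, so a rule that also requires it cannot succeed more often. The same bound applies to a test on T0–T1 change, for each mediator and each contrast.

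**The case against.** The strongest reply is that the trial does examine whether Featback changes the mediators. PTQ and PHQ-4 are secondary outcomes. Table 1 schedules them at T0, T1 and T2 without excluding the WLC, and linear mixed models are planned for effectiveness. A reader might infer that nothing tests the effect of condition on the mediators; the article does not support that. What remains is that the mediation paragraph does not make its claim depend on that result.

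Three other strong readings also fail.

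- A reader might think the missing condition term is itself the defect. The simulation shows that adding it as a covariate cures nothing.
- A reader might compute the chance of a false claim from step two alone. With noncentrality √n × r/√(1 − r²), df = n − 4 and n = 180, partial correlations of 0.15, 0.20, 0.25 and 0.30 give 0.53, 0.78, 0.93 and 0.99. That arithmetic is right, but it leaves out the reverse test, and the correlations have no source in the article: r = 0.10 gives 0.27. If missing monitoring data cut the sample to an assumed 120, r = 0.15 and 0.20 give 0.38 and 0.60.
- A reader might take it as stated that the WLC has no mid-intervention data. This is a strong inference from two sections. Table 1 marks WLC exclusions by a footnote, but not on the weekly monitoring columns.

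It is also fair to say that the mediation paragraph describes its own purpose as temporal order and nowhere says that a significant step two will be declared mediation. That reading comes from joining it to the aim and to the Assessments wording. The article makes that join itself, since it offers no other mediation analysis and does not list this limit in its Discussion.

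**Conclusion.** The concern holds in a limited form. The regressions can establish that early PTQ or PHQ-4 change precedes later SEED change among those who supplied monitoring data. They cannot, by themselves, support the statement that either variable mediates the intervention outcome. Because the article lists the regressors and the safeguard term by term, this is an analysis fixed badly rather than a detail left to a fuller plan.

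Under a natural sequence with no effect of allocation, the criterion is met in roughly 24% to 93% of trials at n = 180, against about 5% without such a sequence. These rates rest on the assumed correlations and cross-lags; that the criterion can be met without any effect of Featback on the mediator does not. The absence of WLC values at week 4 is inferred, but the main point stands without it: with four arms supplying data (n = 240), the criterion as written is still met in 29% to 94% of trials for b = 0.1 to 0.4.

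**What to change.** 1. Describe the cross-lagged result as temporal precedence among Featback users.
2. State that mediation will be claimed only if an effect of condition on T0–T1 change in the same mediator is also shown, and name the contrast that goes with the claim: active conditions versus WLC for Featback itself, or between support levels for the added support. The planned mixed models can supply this test.
3. Reconcile Table 1 with the section on ethical precautions, so that it is clear whether WLC participants complete the weekly monitoring.
4. Optionally, add a supplementary indirect effect of condition based on T0, T1 and T2: condition on T0–T1 mediator change, then T1–T2 SEED change on T0–T1 mediator change with condition and T0–T1 SEED change in the model, and a bootstrap interval for the product. It should stay supplementary. It looks at symptom change after the eight-week intervention, so it could miss a mechanism that has done its work by T1, and its second link is still not randomised.

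The cost is wording and a small amount of analysis. Enrolment is complete, and all the measurements needed are already scheduled. The price is fewer mediation claims and lower power for them, since two links must now be shown instead of one.

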### The Patient Health Questionnaire (PHQ-4)

The PHQ–4 [31] will be used to assess symptoms of depression and anxiety. The PHQ-4 consists of four items: two core anxiety items and two core depression items. Items can be answered on a 4-point Likert scale ranging from 0 ‘not at all’ to 3 ‘nearly every day’. A total score (range 0–12) can be calculated by summing the scores of all four items. Higher scores are indicative of a higher pathology. Factorial and construct validity were demonstrated for the PHQ-4 [31].

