### Perseverative Thinking Questionnaire (PTQ)

The PTQ [32] will be used as a global measure of repetitive negative thinking (e.g., worry and rumination). The questionnaire consists of 15 items assessing the repetitiveness, intrusiveness, difficulties to disengage, and unproductiveness of repetitive negative thinking, as well as the degree to which it captures mental capacity. The scale of the items ranges from 0 ‘never’ to 4 ‘almost always’ and assesses how often each of the characteristics as described above applies to the participants’ thinking process. The Dutch PTQ demonstrated good internal consistency and satisfactory stability [32]. For the current study, we adapted the timeframe from ‘in general’ to ‘in the previous four weeks’ (T0, T1, T2, and T3 assessment) or ‘in the previous week’ (during the intervention period) respectively, in order to increase the ability to detect weekly or monthly change.

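### With one mediator per equation, significant results for both PTQ and PHQ-4 cannot show which of them carries later symptom change; add one joint equation beside the planned ones

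*Protocol article*

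**What the plan says.** The last paragraph of the Background gives the second aim, to study predictors, moderators and mediators "in order to gain insight into when or for whom this intervention works, as well as how it works". Under Assessments, two candidates are named for one outcome: PTQ and PHQ-4 "will be tested as mediators of intervention outcome, being symptoms of ED as measured by the SEED".

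Statistical analyses lists the regressors. The dependent variable is mid- to post-intervention change in the outcome. Step 1 holds early outcome change and "mid- to post-intervention standardized change of the mediator variable as independent variables in the first step". Then: "In the second step, pre- to mid-intervention standardized change of the mediator variable will be entered into the regression equation". The mediator is singular in both steps, and no equation is described that holds PTQ and PHQ-4 together. The one further condition is that the reversed regression, with symptoms predicting the mediator, should not be significant.

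The instrument descriptions show the overlap. The PTQ covers worry and rumination. On the other instrument: "The PHQ-4 consists of four items: two core anxiety items and two core depression items". Both are self-reported, and Table 1 schedules both at T0, at T1 and in the same uneven monitoring weeks.

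**The concern.** Two correlated candidates are each tested without the other. If only one has a direct lagged effect on SEED, the other picks up part of that effect through their correlation, because nothing in its equation removes it. The reversed regression does not address this, since it concerns the direction between symptoms and a mediator and not the overlap between two mediators.

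The mechanism part of the second aim is at stake. If both equations are significant, the natural summary is that both processes mediate. The planned equations cannot distinguish that from one process acting with the other travelling alongside it, or from a sequence in which one leads to the other. The primary comparison of eating pathology between conditions is not affected.

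**Working it through.** **Sample.** The protocol gives no sample size for mediation. Its main chain, taking 79 per group as given, reproduces: 0.75 × 79 = 59.25, taken as 60; 60 × 10/7 = 85.7, taken as 86; 4 × 86 = 344. Weekly monitoring is part of Featback (Basic featback), so mid-intervention data would come from the three active arms: 3 × 86 = 258, and 258 × 0.7 = 180.6, or about 180 after the assumed 30% dropout. That restriction is an inference.

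**Assumptions not in the documents.** All changes are standardised. Early change in each mediator correlates m = 0.3 with early SEED change. Early PTQ and PHQ-4 changes correlate r = 0.3 to 0.7. PTQ has a lagged effect b = 0.1 to 0.3 on late SEED change, and PHQ-4 has no direct effect. The roles can be exchanged.

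**Planned equation for PHQ-4.** Given early SEED change, the slope of PTQ on PHQ-4 is k = (r − m²)/(1 − m²) = (r − 0.09)/0.91. The expected step 2 coefficient of PHQ-4 is b × k. Its standard error is about 1/√(180 × 0.91) = 0.078. For r = 0.5 and b = 0.3: k = 0.41/0.91 = 0.451, the coefficient is 0.135, z = 0.135/0.078 = 1.73, and the chance of two-sided p < 0.05 is about 41%. The same steps give:

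| r | k | b = 0.1 | b = 0.2 | b = 0.3 |
|---|---|---|---|---|
| 0.3 | 0.231 | 6% | 9% | 14% |
| 0.5 | 0.451 | 9% | 21% | 41% |
| 0.6 | 0.560 | 11% | 30% | 58% |
| 0.7 | 0.670 | 14% | 40% | 73% |

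**Simulation.** Simulating the planned regressions gives about 21% to 60% over r = 0.5 to 0.6 and b = 0.2 to 0.3, about 6% to 13% at r = 0.3, and 9% to 14% at b = 0.1 with r = 0.5 to 0.7. A second data model adds a same-period PTQ effect of 0.3 on SEED and requires a non-significant reversed regression. For b = 0.2 and 0.3 it gives 24% and 45% at r = 0.5, 30% and 58% at r = 0.6, and 11% and 18% at r = 0.3.

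**The reversed regression as a safeguard.** In that second model, at r = 0.6 and b = 0.3, it lowers the rate only from 60% to 58%.

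**Joint equation.** With early and late changes of both variables entered, the expected PHQ-4 coefficient is zero, and it is significant in about 4% to 6% of simulated trials. If PTQ reliability is only 0.7 (r = 0.6), 7% to 12% remain.

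**Power cost.** For the variable with the direct effect, z in its own equation at b = 0.2 is 0.2/0.078 = 2.56, or power of about 73%. In the joint equation z is multiplied by √(1 − k²):

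- r = 0.5: 2.56 × 0.893 = 2.29, power about 63%
- r = 0.6: 2.56 × 0.828 = 2.12, power about 56%
- r = 0.7: 2.56 × 0.742 = 1.90, power about 48%

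Simulation agrees: about 72% falls to 63%, 55% and 47%.

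**The case against.** The planned analysis asks whether change in a mediator predicts later symptom change and not the reverse. That is a question about unadjusted prediction and temporal order. In the scenario above, early PHQ-4 change really does predict later SEED change, so a significant result is a correct rejection of the test's own null. A reader might infer that the test fails to hold its 5% error rate. The documents do not support that, because the 5% applies to a null of no contribution given the other mediator, which the protocol does not set. This part of the objection stands: the weakness is a failure to separate the two variables.

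It might also seem to follow that a variable should be called a mediator only on its coefficient adjusted for the other. That goes too far. If change in rumination leads to change in mood, which leads to change in SEED, rumination has no direct effect and yet is a genuine upstream mediator, and the joint equation would dismiss it about 95% of the time. Both changes cover the same interval, so neither model can tell a proxy from an upstream link, and the documents favour neither structure.

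Finally, the article condenses a fuller plan, never says outright that the equations are run separately, and does not exclude a joint model. This stands only in part. The article itself lists the regressors of both steps, in the singular, so the separate reading is the plain one and the choice is open to comment.

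**Conclusion.** The point holds as a limit on interpretation. As written, the equations cannot show whether repetitive negative thinking, depression/anxiety or both carry later SEED change. A variable with no direct effect would be named in about 21% to 60% of trials if overlap is moderate (0.5 to 0.6) and the other variable's lagged effect is 0.2 to 0.3, with about 180 participants.

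A reader might infer that such naming will be common in this trial. The documents do not establish that, since they give neither the correlation nor the effect. With weak overlap or a very small effect the rate is close to nominal or modestly above it. The matter concerns a secondary aim, and the improvement is worth making mainly because it is cheap.

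**What to change.** Keep the planned single-mediator equations. In Statistical analyses, add one equation for late SEED change containing early SEED change and the early and late changes of both PTQ and PHQ-4. Then state three reporting rules:

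- Single-mediator results are described as not mutually adjusted.
- A separate (independent) contribution is claimed for a variable only if its early-change term holds in the joint equation.
- Otherwise, a variable that is significant alone is reported as part of a shared or possibly sequential path.

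The cost is a few sentences and one extra regression on measures the trial already schedules. The joint test loses power as calculated above, and more as overlap grows, so a null joint term should not be read as evidence of no mediation. Some false attribution also remains if a mediator is measured unreliably.
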